**Table 1 Tab1:** Primary, secondary and other objectives and measures in the main trial

Objectives	Outcome measures	Timepoint(s) of evaluation of this outcome measure
Co-primary objectives		
To compare the effect of introducing the behavioural intervention on 30-day mortality post-admission as an acute/general medical inpatient (non-inferiority)	Death, ascertained from hospital records which are routinely updated from national death reporting	30 calendar days after admission to acute/general medicine
To compare the effect of introducing the behavioural intervention on antibiotic exposure per acute/general medical admission (superiority)	Defined daily doses (DDDs) of antibiotics per acute/general medical admission, ascertained from electronic hospital prescribing records	Over each acute/general medical admission, including antibiotics prescribed at discharge
Secondary objectives		
To compare the effect of introducing the behavioural intervention on antibiotic exposure using different metrics	DDD per occupied bed-day, days on antibiotics per admission and bed-day (length of therapy (LOT)),^a^ antibiotic days per admission and bed-day (days of therapy, DOT^a^), carbapenem DDD, DOT^a^ and LOT^a^ (per admission and per bed-day), broad-spectrum DDD, DOT^a^ and LOT^a^ (per admission and per bed-day), IV and oral DDD, DOT^a^ and LOT^a^ (per admission and per bed-day), WHO-defined ’Access’, ’Watch’ and ’Reserve’ DDD, DOT^a^ and LOT^a^ (per admission and per bed-day), ’Access’ as a percentage of all antibiotic use	Over each acute/general medical admission, including antibiotics prescribed at discharge
To compare the effect of introducing the behavioural intervention on adverse outcomes	ICU admission during the current admission, total length of stay (hours), antibiotic restart after discontinuation,^a^ emergency re-admission in the 30 days after discharge, *C. difficile* diarrhoea, mortality over the longer term	ICU admission over the current admission; for emergency re-admission, up to 30 days post-discharge; for *C. difficile* diarrhoea, up to 90 days post-admission; for mortality up to 90 days post-admission
To evaluate the impact of the intervention on the faecal flora	Proportion of discarded faecal samples from medical inpatients from which extended spectrum beta-lactamase (ESBL)-carrying *Enterobacteriaceae* can be isolated	Repeated cross-sectional surveys over time
Tertiary objectives		

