To evaluate the cost-effectiveness of the behavioural intervention	Resource utilisation and costs	Over the current admission and up to 30 days post-discharge
To quantify uptake and acceptability of the online training component of the behavioural intervention (process outcome)	Proportion of locally identified and pre-specified essential individuals who drive prescribing decisions for acute/general medical inpatients at the organisation who complete the online training (recorded electronically by individuals entering their name and work (NHS) email on the last page) or on an attendance list if the local organisation has opted to do face-to-face training sessions	Within 3 months of invitation to complete training
To quantify uptake of the ARK ‘review and revise’ procedure within the behavioural intervention (process outcome)	Proportion of regularly audited antibiotics prescriptions which document the ARK classification criteria Proportion of regularly audited antibiotics prescriptions which are stopped at ‘review and revise’	Over 12 weeks following implementation date

^a^In organisations with individual electronic prescribing (rather than bulk) antibiotic data

Note: WHO definitions of ’Access’, ’Watch’ and ’Reserve’ antibiotics will be used, following the 2017 Essential Medicines List, using the PHE interpretation. Broad-spectrum is defined as co-amoxiclav; piperacillin/tazobactam; second (e.g. cefuroxime), third (e.g. ceftriaxone ceftazidime) or fourth (e.g. cefepime) generation cephalosporins or cephalosporin-beta-lactamase inhibitor combinations (e.g. ceftazidime-avibactam, ceftolozane-tazobactam); carbapenems; quinolones; azithromycin; tigecycline; aztreonam; and telithromycin. Cefaclor is not included as a second generation cephalosporin because it is administered orally and is not well absorbed

Process evaluation will also include interviews/focus groups with healthcare professionals, a brief questionnaire concerning healthcare professionals’ perceived barriers to review and revise (collected online on completion of the online training and 1 month later) and healthcare professionals’ usage of the online training (collected automatically by the website and mobile software). Implementation of ARK will also be assessed using a questionnaire completed by the ARK champion.

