DDDs using standard WHO formulae (www.whocc.no) are designed to transform milligrams of different antibiotics into standard units reflecting a typical dose and are recommended for use in antibiotic evaluations [52]. Their most important limitation is that reducing prescribing of broad-spectrum antibiotics often involves moving to a combination of multiple agents of narrower spectrum. A single DDD of a broad-spectrum antibiotic may therefore be replaced with multiple DDDs of narrower spectrum antibiotics, but this is probably better for future antimicrobial resistance. For this reason, where organisations are able to provide individual-level antibiotic prescribing data, we will also analyse length of therapy (LOT), defined as the time (days/hours/minutes) between the last and first administration of antibiotic treatment (lumping all antibiotics together), and days of therapy (DOT), defined as the sum of the time (days/hours/minutes) between the last and first administration of each separate antibiotic. However, relatively few organisations currently have individual-level electronic prescribing systems, and therefore most are only able to provide bulk-level DDDs in acute/general medical inpatients.

Admission (rather than bed-day) is the denominator for antibiotic usage (similar to the UK DH Antimicrobial Prescribing Quality Measures), because bed-day can be strongly influenced by non-medical reasons for not discharging inpatients. However, this provides a challenge since it is not straightforward to identify these admissions from the electronic inpatient admission records (see the preceding discussion). Where hospitals provide data on bulk prescriptions only (e.g. using the JAC or Rx-info systems), they are able to provide both total DDDs and DDDs per admission to the relevant hospital areas. The primary analysis will use this denominator wherever available. Where these data are not available, we will use estimates of the relevant admissions and overnight stays from the population defined above.

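### LOT and DOT are defined as the time from first to last dose, which is not the count of antibiotic days that Table 1 names and gives no rule for discharge antibiotics

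*Protocol article*

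**What the plan says.** The text of Outcomes and their assessment gives an explicit rule for each measure. LOT is "defined as the time (days/hours/minutes) between the last and first administration of antibiotic treatment (lumping all antibiotics together". DOT is "the sum of the time (days/hours/minutes) between the last and first administration of each separate antibiotic". No final day or dosing interval is added, single doses have no minimum value, and gaps in treatment are not mentioned.

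Table 1 describes the same two measures differently, as "days on antibiotics per admission and bed-day (length of therapy (LOT" and "antibiotic days per admission and bed-day (days of therapy, DOT^a". Their time window is "Over each acute/general medical admission, including antibiotics prescribed at discharge". A separate secondary outcome is "antibiotic restart after discontinuation", so the plan expects some courses to stop and start again. Footnote a of Table 1 limits LOT and DOT: "In organisations with individual electronic prescribing (rather than bulk) antibiotic data". The text adds that few organisations have such systems at present.

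Under Statistical analysis, antibiotic outcomes other than DDDs are to be analysed by ordinal logistic regression, or by linear regression if the data are approximately normal, with or without transformation.

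**The concern.** Elapsed time between two doses and a count of days on treatment are different quantities. They part company in the situations that this intervention is likely to create: very short courses after an early stop, courses stopped and then restarted, and one drug replaced by another. The last matters most for DOT, because the article introduces LOT and DOT to deal with the weakness of DDDs when one broad-spectrum drug is replaced by several narrower ones.

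LOT and DOT are the direct measures of treatment duration among the antibiotic outcomes. Table 1 repeats them for carbapenems, broad-spectrum drugs, intravenous and oral use, and the WHO groups, so one rule feeds many secondary results.

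**Working it through.** **Inputs from the article:** the two definitions, the Table 1 labels and window, the restart outcome and the planned models. **Assumptions, not in the article:** regular dosing every τ hours, courses of 1 to 7 days, and the gap lengths and splits shown below. There is no figure in the plan to reproduce. The stated rule is simply applied.

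**1. Lost interval.** A course of D days has n = 24D/τ doses, so last minus first = (n − 1)τ/24 = D − τ/24 days.

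| τ (hours) | D = 1 | D = 3 | D = 7 |
|---|---|---|---|
| 6 | 0.75 | 2.75 | 6.75 |
| 8 | 0.67 | 2.67 | 6.67 |
| 12 | 0.50 | 2.50 | 6.50 |
| 24 | 0 | 2.00 | 6.00 |

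As a ratio, a cut from 7 to 3 days is 1 − 3/7 = 57%. The rule reads it as 59%, 60%, 62% and 67% for τ = 6, 8, 12 and 24. The planned models do not work on that ratio. At a common τ the shift is constant, so the rank order of treated courses is unchanged (ordinal model) and the difference is unchanged (untransformed linear model: 6.67 − 2.67 = 4 = 7 − 3). This part largely cancels. Steps 2 to 4 do not.

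**2. Single dose.** The first and last doses coincide, so LOT = DOT = 0. The course ties with an untreated admission in an ordinal model and is indistinguishable from it in a linear one.

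**3. Stop and restart.** Three days on, two days off, three days on gives 6 treated days.
- LOT = 3 + 2 + (3 − τ/24) = 7.67 (8-hourly) or 7.00 (once daily).
- An uninterrupted 7-day course scores 6.67 or 6.00.
- The true difference is 6 − 7 = −1 day, and the rule reads +1 day. The ranking is reversed, so neither model removes the error.
- DOT equals LOT here if the same drug restarts (7.67 or 7.00). If a different drug restarts, DOT = 2(3 − τ/24) = 5.33 or 4.00, and the gap is left out.

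With treatment on days 1–2 and 6–10 (7 treated days), LOT is 9.67 (8-hourly) or 9 (once daily).

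**4. Change of drug.** Take 7 treated days in each case.
- Once daily: one drug scores 7 − 1 = 6. Three days on A and then four on B score (3 − 1) + (4 − 1) = 5, which is 1/6 = 17% lower.
- 8-hourly: 6.67 against 2.67 + 3.67 = 6.33 (6.333 before rounding), which is 0.333/6.667 = 5% lower.

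DOT falls although the number of antibiotic days is the same.

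**5. Discharge antibiotics.** Table 1 includes them. The text measures between administrations and does not say how a discharge prescription becomes a duration. If only in-hospital administrations were used, 2 inpatient days plus a 5-day discharge course would score 1.67 (8-hourly) or 1.00 (once daily) instead of 7. That shows what depends on the missing rule. It is not a prediction of what the trial will do.

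**The case against.** The case against has several parts.

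- **The lost interval is harmless under the planned models.** This stands for treated courses on one drug at a common dosing interval (step 1). A reader might infer that reductions will be inflated to 60–67%. The documents do not support that, because those figures are ratios under assumed intervals and the planned models do not use that ratio. The argument does not cover single doses, gaps or changes of drug.
- **Discharge courses do not drop out.** This also stands. A reader might infer that they do, but Table 1 says they are included, and the data specification is not shown. What remains is a conflict between Table 1 and a definition that offers no way to count them.
- **Gaps do not always enter DOT.** Correct: they enter only when the same drug restarts.
- **Continuous time looks deliberate, and calendar days have their own error.** The wording does allow hours and minutes. Calendar days are coarser: doses at 23:00 and 07:00 count as 2 days. But the deliberate choice still contradicts the day counts named in Table 1.
- **Handling rules belong in the SAP.** That would answer a missing detail. Here a rule is stated, and followed literally it gives the values above.
- **The reach is small, and restarts and stopping at review are recorded elsewhere.** True. This limits the importance of the point but does not make the definition right.

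**Conclusion.** The point holds in a limited form. The stated definitions of LOT and DOT do not produce the antibiotic days that Table 1 names. Three errors survive the planned models: single-dose courses score 0, untreated gaps count as LOT (and as DOT if the same drug restarts), and DOT loses one dosing interval for each drug used. The definition and Table 1 also need to be reconciled on discharge antibiotics.

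The examples range from a 5–17% fall in DOT with no change in antibiotic days to a stop-and-restart course of 6 treated days that scores above an uninterrupted 7-day course. They all rest on assumed dosing intervals, course lengths and gaps. A reader might infer that the rule favours the intervention. The documents do not show this: lost intervals and zero scores lower the measured duration, counted gaps raise it, and no restart frequency, gap length or distribution of course lengths is given. Neither the size nor the net direction of bias can be derived.

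The effect is confined to secondary outcomes in organisations with individual-level prescribing data. Both co-primary outcomes, 30-day mortality and DDDs per admission, are untouched. It should be corrected before analysis, but it does not threaten the main conclusions.

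**What to change.** Replace the two definitions and align them with Table 1:

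- LOT: the number of calendar days on which at least one dose of any antibiotic was given.
- DOT: the sum over drugs of the calendar days on which at least one dose of that drug was given.
- Discharge antibiotics: either add the prescribed discharge days by a stated rule, or restrict LOT and DOT to inpatient treatment and correct the Table 1 window for them.

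A single dose then counts as 1 day, untreated days count as 0, and seven days split over two consecutive drugs without overlap still count as 7. If the SAP already counts days in this way, only the protocol text needs correcting.

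The cost is a change of wording in the protocol and SAP, and a different calculation on the same administration records. The inpatient part needs no new data. Adding discharge days would need the length of supply from the discharge prescription. The small drawback is a coarser measure that can round up courses crossing midnight.

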### Statistical analysis

Analyses will be presented for all organisations. However, the primary analysis will include only the pilot and main trial trusts (the pilot trusts are included to maximise power and because the intervention was essentially unchanged between the pilot study and the main trial, and the pilot study sites did not choose their implementation dates). A sensitivity analysis of the primary outcomes will include the main trial sites only. If results provide a qualitatively different interpretation, these sensitivity analyses will be conducted for all outcomes.

The primary analysis method for binary outcomes will be logistic regression. This is done because, for mortality, data will be considered to be completely ascertained on the basis of routine checks that each organisation conducts against the national death registry, for example, to ensure that follow-up letters are not sent to patients who have died. Therefore, patients not recorded as dying in the national system will be assumed to be alive 30 days (co-primary outcome) and 90 days (secondary outcome) after admission. The death registry is not up to date in real time, and routine checks are only carried out periodically; the final data extract will be requested 6 months after the last included admission to ensure that ascertainment is as robust as possible. In-hospital mortality is completely ascertained by discharge codes. Further, for all binary outcomes, event rates are relatively low (5–10%), so there is little difference between analysing a cause-specific hazard or a competing risks subhazard. Analysing the outcome using logistic regression also facilitates visualisation of the estimated pre- and post-implementation trends, and the step change at implementation, against the observed percentages for each outcome per organisation. Sensitivity analyses will consider these as time-to-event outcomes and will consider competing risks from inpatient and out-of-hospital deaths as relevant for each specific outcome [53–55]. Negative binomial regression will be used to model antibiotic DDDs, incorporating over-dispersion and using different offsets as defined previously. Other antibiotic outcomes are planned to be analysed using ordinal logistic regression; however, if, for example, data are approximately normally distributed, either before or after transformation, linear regression may be used instead. Box-Cox-transformed length of stay will be analysed using normal linear regression. A sensitivity analysis will include stay only up to the point a patient was declared medically fit for discharge. A second sensitivity analysis will use quantile regression of the 90th percentile to assess effects at the extremes of the distribution.

For analyses comparing periods before and after introduction of the intervention, we hypothesise that the intervention could produce either a step change in each outcome, or ongoing changes over time (i.e. an interaction between intervention vs control and calendar time), or both. Analysis will therefore use an interrupted time series (ITS) analysis which not only estimates whether the intervention has a direct immediate impact, but also whether it has any impact on year-on-year trends after implementation (and compared with year-on-year trends pre-implementation) (Fig. 2). For example, even if there is no immediate impact of the intervention on mortality, it will be particularly important to monitor, say, whether any calendar year trends suggest mortality increases post-implementation. It will also be important to monitor whether antibiotic use declined faster post- vs pre-implementation.

Other reasons for using the ITS approach within organisation, and then pooling organisation-level estimates, are that many other things are likely to be changing differently in different organisations, and within organisations, over calendar time. For example, financial incentives could be introduced to reduce antibiotic use in hospital and increase the numbers of antibiotic prescriptions that receive review (under the Commissioning for Quality and Innovation [CQUIN]) payments framework). These external factors will affect within-organisation comparisons less than between-organisation comparisons. Further rates may not be constant before or after the intervention. Finally the calendar-time blocked randomisation makes the assumptions underlying the standard vertical comparisons (between organisations already randomised to intervention vs not at each step) more questionable. The date of introduction of the intervention will be the planned date of implementation for the feasibility and internal pilot organisations and the date that each organisation was randomised to implement the intervention in the main trial. Sensitivity analyses for the main trial will also consider the fact that implementation may occur gradually over approximately 3 months [56], by incorporating a trend for the 3 months post-implementation date instead of a single step change at the implementation date. The DMC will be asked to advise on the most appropriate analysis model as part of their Charter.

Each outcome will first be modelled separately in each organisation, estimating trends before and after intervention implementation, plus an implementation-associated immediate effect (‘step change’) (Fig. 2). The unit of analysis will be admission. Patient will be used as a clustering variable for robust variance adjustment (but not otherwise adjusted for). Based on data available to date, we do not expect strong seasonal effects in the outcomes above, but this will be investigated and included if necessary. Meta-analytic techniques will then be used to combine these organisation-specific estimates to produce an overall intervention effect, assessing heterogeneity using *I*^2^ statistics. This approach is similar to a multilevel model, but it has more flexibility in modelling individual organisations. The primary comparison will be a 2 degree of freedom test, jointly testing that the ‘step change’ is zero and that there is no change in calendar trends post- vs pre-implementation. This joint test will be fitted on model parameters and explicitly account for correlation between the two estimands. Secondary analyses will consider calendar trends post-implementation, and change in calendar trends post- vs pre-implementation, and a trend for implementation over 3 months rather than a ‘step change’.

The major concern about unadjusted analyses is the potential for variation in case mix, particularly over a calendar year, to affect estimates of intervention effect. Additional sensitivity analyses will adjust for case mix to assess whether changes in case mix could confound any changes in antibiotic use observed over time. The following admission-level covariates have been chosen based on their significant effects on 30-day mortality in previous analyses of emergency admissions from routinely collected data [57] and will be adjusted for in each organisation regardless of statistical significance (with non-linear relationships between covariates and outcomes assessed and incorporated using natural cubic splines): sex; age (years) at admission; immunosuppression; Charlson Co-Morbidity Index (defined using secondary diagnosis codes); interaction between age and Charlson [57]; patient classification; admission method, source, specialty, day of the week, time of day and day of year and interaction between admission day of the week and time of day [57]; number of admissions in previous year (excluding as day case), and ever had a complex admission.

All analyses will be modified intention-to-treat, including all randomised organisations who attempted to implement the intervention but excluding any organisations who withdrew between randomisation and randomised implementation date (who therefore never attempted to implement the intervention and in whom effects will be null by definition). It is not possible to specify an individual-level per-protocol population since the precise method of management of each individual inpatient is unknown. All results will be interpreted in the light of the changes in antibiotic use achieved, both overall and by organisation. At the organisation level, a per-protocol population will be defined broadly by > 50% of locally identified and pre-specified essential individuals who drive prescribing decisions for acute/general medical inpatients having accessed the online training (recorded electronically by individuals entering their name and work (NHS) email on the last page or on an attendance list if the local organisation has opted to do face-to-face training sessions). More specifically, we specify eight criteria defining implementation fidelity:Provision of a list of key essential people, by implementation dateAchieving at least 20 people per 100 acute beds who have done the online learning, by end of implementation dateIntroduction of the ARK categories into the prescribing process, generally by adjusting the physical drug chart or e-prescribing system. As a minimum, documentation of categories into clerking or system to force stop/re-prescribe by 72 h in e-prescribing, by implementation dateProcess in place for making patient leaflet available to acute medical patients, by implementation dateSubmission of baseline audit data, by implementation dateProcess in place for ongoing audit and feedback, by implementation dateSubmission of initial post-implementation audit data, by week 4Submission of electronic patient research data, by week 16 following implementation

Failing to meet five or more criteria would be considered a failure to implement in analysis.

Intervention uptake will be assessed by estimating the proportion of locally identified and pre-specified essential individuals who drive prescribing decisions for acute/general medical inpatients at the organisation who complete the online training.

Process evaluation analyses will seek to better understand how ARK was implemented across different hospitals, potential barriers and facilitators and also how implementation influenced use of the intervention and antibiotic use. This will be triangulated with data from qualitative interviews/focus groups, which will undergo thematic analysis. Secondary analyses will consider how much of any effect of the intervention could be mediated through different aspects of the implementation of review and revise, including training completion rates, evidence of implementation from audit records as well as success of implementation in each hospital, based on mixed methods evaluation and documentary evidence, and number of the preceding criteria met.

For the primary endpoint, subgroup analyses will be conducted by investigating heterogeneity in the organisation-level intervention effect estimates across the following factors, using meta-regression techniques: randomisation block (categorical stratification factor), calendar period of randomised implementation date (reflecting different NHS pressures) (Jan–Mar, Apr–Jun, Jul–Sep, Oct–Dec), organisation type (small, medium, large, teaching), region, functional role of champion (acute medicine, microbiology/infectious diseases, pharmacist), paper vs electronic prescribing systems, percentage of essential people completing training by 12 weeks, total number completing training by 12 weeks per 100 acute beds.

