To avoid contamination, complete information about the intervention is released to the local champion at the point of randomisation, which is 3 months before anticipated organisation-wide implementation. The intervention is not blinded; patients who receive the leaflet or who are aware of study posters will also not be blinded.

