### Randomisation

The phase III main trial uses an organisation-randomised stepped-wedge design in which interventions are successively implemented across different organisations over time.

The stepped-wedge cluster-randomised main trial uses calendar-time blocked randomisation. The randomisation list was drawn up in blocks of 6 before the trial started. Organisations were added to a separate list of trial sites based on the date when they joined the ARK network, divided into groups of 6, with the implementation date for each organisation then randomly assigned by the randomisation list (i.e randomisation stratified by these blocks). This is feasible, because all research data on which the intervention is evaluated are routine electronic health record data that are completely independent of the trial. Thus, they are available historically and collected in the same way, regardless of the date of randomisation/implementation— there are no research-specific outcome data in the trial (details in a subsequent section). Organisations have no control over which block they are allocated to or to their randomisation date: 24 organisations had already joined the network at the start of randomisation. This was a pragmatic decision based on the fact that trusts in the main trial would be randomised over 18 months, and in the current NHS climate it is impossible to get NHS trusts to agree to join a programme to reduce antibiotic use where they might not get the intervention for 18 months. All comparisons will be made before and after implementation in the same trust (see the following paragraphs), since any comparison across trusts pooling time will be irretrievably confounded by various organisational changes internally and externally.

In practice, the local champions need some lead time to get an implementation team together, to identify the essential individuals who drive prescribing decisions for acute/general medical inpatients at the organisation (in whom training uptake will be assessed) and to arrange meetings with staff before implementation. Randomisation therefore occurs 3 months before the target ‘implementation date’ (baseline), and the implementation toolkit contains a focused set of activities from this randomisation date through to implementation.

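### The time-series break sits at the implementation date and no stated analysis sets aside the three-month lead-in, so any prescribing change in it dilutes the step and makes mortality non-inferiority somewhat easier to claim

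*Protocol article*

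**What the plan says.** **What happens before the date.** Under Intervention, "complete information about the intervention is released to the local champion at the point of randomisation, which is 3 months before anticipated organisation-wide implementation". Under Randomisation, "the implementation toolkit contains a focused set of activities from this randomisation date through to implementation". The fidelity criteria under Statistical analysis set several things to be achieved by the implementation date. One is "at least 20 people per 100 acute beds who have done the online learning". Another is that the ARK categories are in the prescribing process, "generally by adjusting the physical drug chart or e-prescribing system". A leaflet process, baseline audit data and an audit-and-feedback process are due by then as well.

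**Where the analysis cuts.** The introduction date for main-trial sites is "the date that each organisation was randomised to implement the intervention in the main trial". Each organisation is modelled separately, "estimating trends before and after intervention implementation, plus an implementation-associated immediate effect", and the estimates are pooled by meta-analysis. The primary comparison is a joint 2-degree-of-freedom test of step and slope change.

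**Timing alternatives.** The sensitivity analysis handles gradual uptake "by incorporating a trend for the 3 months post-implementation date instead of a single step change at the implementation date". A secondary analysis replaces the step with an implementation trend over three months, without saying that this covers time before the date. The article states no analysis that excludes the lead-in or models it separately.

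**The concern.** Training, the decision aid, data collection on review and stopping, and the leaflet are all listed as components of the intervention. Training a fifth as many people as there are acute beds, and completing a baseline audit, cannot all fall on one Monday. Some intervention activity therefore precedes the break point.

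If that activity changes prescribing, the affected months are the last points of the pre-implementation segment, where they pull hardest on the projected counterfactual. The step shrinks and the pre-trend tilts towards the effect, so the post-implementation trend appears to wane.

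The two co-primary outcomes are affected differently. For antibiotic use, dilution works against the trial's claim. For mortality, harm that began in the lead-in is absorbed into the baseline, which makes it easier for the confidence interval to lie within [0.95, 1.05].

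**Working it through.** **The plan's own figure.** Sample size states more than 85% power with 36 organisations. Simulation with 24 months of history, the step-plus-trend model and a monthly mortality SD of 0.001 or 0.01 gave 98% or 91% for non-inferiority and about 100% for DDDs, consistent with the claim. With the SD of 0.1 read literally as a probability, and dispersion read as variance = mean + 1.15 × mean², the figures were about 23% and 44%. The inputs are too ambiguous to confirm the stated power, and nothing below depends on it. The described simulation includes no lead-in exposure.

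**Inputs from the article.** Data start on 1 February 2016. Main-trial implementation runs from 12 February 2018 to 24 June 2019, followed by 12 months of follow-up. Main-trial sites thus have about 24–41 pre-implementation months. Sites have 5,000–15,000 admissions a year plus one of 25,000, mortality is 7–10%, and the margin is 0.95–1.05.

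**Assumptions.** The spread of the 36 implementation months, no true slope change, the share of the full effect present in the last three pre-months, and non-inferiority judged on the step.

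**Hand check of the leverage.** Take n = 32 pre-months, numbered 0 to 31. The mean is 15.5 and Sxx = n(n² − 1)/12 = 2728. The line projected to the break (31.5) gives month i the weight 1/n + (31.5 − 15.5)(i − 15.5)/Sxx. The last three months get 0.110, 0.116 and 0.122, about 0.35 together.

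- If the effect builds linearly to full, the three months carry 1/6, 1/2 and 5/6 of it. Step lost = 0.110/6 + 0.116/2 + 0.122 × 5/6 ≈ 0.18.
- The pre-slope is tilted by 12 × (13.5/6 + 14.5/2 + 15.5 × 5/6)/2728 = 0.099 of the full effect per year. Times |ln 0.85| = 0.1625, that is about 1.6% a year for DDDs.

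**Pooled over 36 organisations** by inverse variance (SE of the mortality step 0.0109). With k the fraction of the step kept, the DDD ratio is 0.85^k and the mortality odds ratio is 1.05^k. The chance of passing is Φ[(ln 1.05 − 1.96 × 0.0109 − k ln 1.05)/0.0109].

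| Lead-in profile | Mean exposure | Step kept | 15% DDD reduction seen as | False DDD slope change per year | OR 1.05 seen as | Upper limit < 1.05 at true OR 1.05 |
|---|---|---|---|---|---|---|
| None | 0 | 100% | 15.0% | 0 | 1.050 | 2.5% |
| Builds to 25% | 12.5% | 96% | 14.4% | +0.5% | 1.048 | 3.8% |
| Builds to 50% | 25% | 92% | 13.8% | +0.9% | 1.046 | 5.7% |
| One third throughout | 33% | 89% | 13.5% | +1.2% | 1.044 | 7% |
| Builds to 100% | 50% | 83% | 12.6% | +1.8% | 1.041 | 11.4% |
| Full throughout (bound) | 100% | 67% | 10.3% | +3.6% | 1.033 | 31.4% |

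The one-third row is a third of the bias in the bound: 32.8%/3 = 10.9% lost, and log slope 0.0349/3 = 0.0116.

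**At 12 months, building to 100%.** DDD ratio 0.874 × 1.018 = 0.890, an 11.0% reduction. The mortality slope is 0.0178 × 0.0488/0.1625 = 0.0053 on the log scale, so 1.0414 × e^(−0.0053) = 1.036.

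**Does the planned post-date ramp help?** No. At 50% mean exposure its step stays at 83%. Its false slope change is larger (+0.037 log units a year), but part of that comes from fitting a ramp to an effect already complete at the date. The step is the relevant comparison.

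**Leaving out the three months** restores the step to 100% and the slope change to 0 in every row. The SE rises from 0.0109 to 0.0118 (0.0118/0.0109 = 1.08). Repeat projections with other assumed implementation months put the rise at 9–10% and the step kept at 82% for the linear build-up to full.

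**The case against.** The strongest reply is that an effect before the date is inferred, not documented. Materials go to the champion, not to prescribers. The lead time is described as assembling a team, identifying essential people and arranging meetings. Criteria are due by the date, so a chart changed that day qualifies. Two criteria ask only for a process in place, and a baseline audit need not alter prescribing. The uptake measures for ARK classification and stopping cover the 12 weeks after the date, and the plan itself expects gradual uptake over about three months afterwards. This stands: exposure is unknown and could be small. Building to full by the date is the severe end, because it leaves nothing for the expected later ramp. Pre-date training is the main evidence the other way.

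A reader might infer that a true 5% mortality increase, seen as about +4.1%, would slip inside the margin. The article does not support that. The whole 95% interval must lie within the margin, so with an SE of 0.0109 the estimate must be below exp(0.0488 − 0.0214) = 1.028. An average estimate of 1.041 would still fail about 89% of the time.

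It is also fair that the randomised date is a fixed, defensible cut-point, that the DMC is asked to advise on the model, and that the unseen analysis plan may hold more timing analyses. But this article fixes the cut-point and describes a timing sensitivity analysis in one direction only.

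**Conclusion.** The point holds in conditional form. The break point treats the whole lead-in as control time, and the stated timing alternatives do not address it. To the extent that prescribing changes in those months, the step is attenuated by about 4–17% over a plausible range. The 12-month effect is attenuated too, and a false slope change is added. That slope term belongs to the joint test and moves away from zero when its true value is zero, so it would be wrong to say that everything shrinks towards zero.

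For DDD superiority the bias is conservative. For mortality it raises the false non-inferiority rate at the margin from 2.5% to roughly 4–11%. These figures rest on assumed exposure profiles and implementation months, no true slope change, and a decision on the step. The article does not establish that the effect begins in the lead-in, or that harm would routinely pass. This is a cheap improvement worth making, not a flaw that invalidates the design.

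**What to change.** For both co-primary outcomes, pre-specify an interrupted time series that omits the interval from randomisation to randomised implementation, or gives it its own transition segment. Require the mortality non-inferiority conclusion to hold in this analysis as well as in the implementation-date model. Alternatively, make it primary and keep the present model as the sensitivity analysis.

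Use each site's actual dates instead of a uniform three months. The two main-trial examples under Main trial status span 13 weeks (13 November 2017 to 12 February 2018) and 12 weeks (1 April to 24 June 2019). Pilot sites, which are in the primary analysis, need their own materials-release dates. These are not in the article, and preparation was set at four months under protocol version 2.0 and returned to three only in version 4.0.

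The cost is an 8–10% larger standard error on the step, some extra analysis, and retrieval of the pilot dates. No new outcome data are needed.
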